#### Exclusion criteria

Instability of general clinical conditions (mechanical ventilation, sedation, sepsis, sub-emergent epileptic seizures).UWS, according to the Coma Recovery Scale – Revised (CRS-R) (40).Known fear of needles (agophobia), as reported by the patient’s legal representative.

Patient’s legal representatives will receive written and oral information about the study aims, interventions, potential risks, and rights. Informed consent will be obtained before enrollment. All subjects will undergo an initial evaluation (T0), an evaluation at 4 weeks (T1) and a follow-up at 3 months (T2) (see Figure 1).

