### Randomization, allocation concealment and blinding

After enrollment, patients will be allocated to one of two groups by computerized randomization and stratified by MASA scale, with an allocation ratio of 1:1, and assigned to either the control or intervention arm. Allocation concealment will be ensured via sequentially numbered, opaque, sealed envelopes prepared by an independent statistician (see Figure 2). The study is designed as double-blind: all clinical and instrumental assessments will be performed by professionals blinded to the treatment arm, and patients are considered blinded either because they present a DoC or due to severe cognitive impairment with short-term memory deficits, which prevent them from being aware of or recalling the treatment received. Due to the nature of the acupuncture intervention, blinding of the acupuncturist is not feasible and represents a potential source of performance bias. To minimize its impact, several mitigation strategies were implemented *a priori*. Acupuncturists will not be involved in outcome assessment, rehabilitation planning, or data analysis. The intervention will be delivered according to a standardized protocol, including fixed session duration, predefined acupuncture points, and uniform treatment setting. Outcome assessors and the rehabilitation team will remain blinded to group allocation throughout the study. Any accidental unblinding will be documented.

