### Outcome measures

The primary outcome is the improvement of dysphagia and will be measured using the MASA scale (53, 54) and the instrumental scale “Rationale scores based on endoscopic landmarks and bedside parameters” with relative values (43) at T1. The same scales will be used at T2 to measure the maintenance of the effect.

Secondary outcomes include: (1) improvement on the decannulation rate and/or reduction in decannulation timings at T1 and T2; (2) reduction of the rate of infections at T1 and T2; (3) improvement on functional autonomy measured by the GOS-E at T2.

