### Statistical analysis

At present, we have designed a pilot study with the purpose of providing preliminary data necessary to calculate the appropriate sample size for a subsequent randomized controlled trial (RCT). The main study will be a 2-arm, randomized, controlled trial for which a medium effect size was conservatively hypothesized. According to the stepped rules of thumb proposed to estimate the size of the pilot based on Cohen’s d effect size (55), for an 80% power main trial, the pilot sample size should be 10 per arm, and the subsequent main trial will require somewhere between 34 and 176 participants per arm. The sample size of 10 participants per arm will be increased to 12 participants per arm to account for potential dropouts. This sample size was determined exclusively since methodological recommendations available in the literature. The data obtained from this pilot study will be used to estimate the effect size and variability, which will inform the power analysis and the determination of the required sample size for the definitive RCT. Analyses will be conducted using SPSS version 28 software (SPSS, SPSS Inc., Chicago, United States). The normality of the distribution of continuous variables will be checked using the Shapiro–Wilk test. If the variables violate the assumption of normality, they will be presented through their median value and interquartile range, otherwise through mean and standard deviation. Categorical variables will be represented through absolute frequencies and percentages. Baseline characteristics will be compared between treatment and control groups using independent *t*-tests or Mann–Whitney U tests for continuous variables, depending on data distribution, and chi-square or Fisher’s exact tests for categorical variables. The primary outcome (improvement in dysphagia) will be assessed by comparing MASA scores and “Pooling score” between groups at T1 using ANCOVA models (adjusting for baseline values) or non-parametric alternatives, if assumptions are not met. Maintenance of the effect at T2 will be evaluated using linear mixed models with random intercepts, including group, time (baseline, T1, T2), and their interaction as fixed effects; if model assumptions are violated, change scores between T1 and T2 will be calculated and compared between groups using independent *t*-tests or Mann–Whitney U tests. Secondary outcomes will be analyzed as follows: decannulation rates at T1 and T2 will be compared between groups using chi-square or Fisher’s exact tests, while decannulation times will be compared using independent *t*-tests or Mann–Whitney U tests and Kaplan–Meier survival analysis. Infection rates at T1 and T2 will be compared between groups using chi-square or Fisher’s exact tests. Functional autonomy at T2, measured by the GOS-E, will be compared between groups using independent *t*-tests if normality assumptions are met, or Mann–Whitney U tests otherwise. A *p*-value <0.05 will be considered significant in all analyses. The primary analysis will follow the intention-to-treat (ITT) principle. Sensitivity analysis will be performed to assess the robustness of the findings, including per-protocol analysis restricted to patients who completed the assigned intervention.

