Auriculotherapy involves stimulation of specific points on the auricular pavilion, considered a major microsystem of the body (67). From a Western medical perspective, its effects are understood through neurophysiological and reflexogenic mechanisms (67), as the ear receives extensive innervation from four mixed cranial nerves—trigeminal, facial, glossopharyngeal, and vagus nerve—as well as from the cervical plexus (C2/C3) (68). To date, no studies have specifically investigated auriculotherapy in patients with sABI, and only limited evidence exists regarding its use in post-stroke dysphagia. Together, these points provide a multi-target approach that combines peripheral sensorimotor facilitation with central autonomic modulation. This strategy aligns with evidence suggesting that auricular stimulation may activate brainstem nuclei—such as the nucleus tractus solitarius and nucleus ambiguus—and support neuroplasticity in neurorehabilitation. The inclusion of multiple auricular points in our protocol was also motivated by practical considerations related to the clinical condition of sABI patients. Severe motor impairments, abnormal postures, spasticity, and involuntary movements often hinder access to body acupuncture points, compromising safety and feasibility. In contrast, the auricle provides a compact, easily accessible surface where stimulation can be safely administered with minimal repositioning, even in bedridden or low-responsive patients. This anatomical and logistical advantage makes auriculotherapy particularly well-suited for complex neurorehabilitation contexts. Finally, the effectiveness of somatic and auricular acupuncture will be evaluated using a treatment schedule aligned with evidence-based protocols reported in the literature (29). The persistence of treatment benefits will be assessed at follow-up (T2), conducted 2 months after the conclusion of acupuncture therapy, during which patients will continue to receive standard rehabilitation care.

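### Neither the three-visit group-by-time interaction nor its fallback change-score test answers whether the T1 benefit is still present at T2; a baseline-adjusted T2 difference should be named

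*Protocol article*

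**What the plan says.** Patients are assessed at baseline, with "an evaluation at 4 weeks (T1) and a follow-up at 3 months (T2"). Under Outcome measures, the primary time point is T1, and for the later visit the protocol states: "The same scales will be used at T2 to measure the maintenance of the effect". The Discussion gives the sense of this: "The persistence of treatment benefits will be assessed at follow-up (T2), conducted 2 months after the conclusion of acupuncture therapy".

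The Statistical analysis section compares MASA and Pooling scores at T1 by ANCOVA adjusted for baseline. For T2 it changes method: "Maintenance of the effect at T2 will be evaluated using linear mixed models with random intercepts, including group, time (baseline, T1, T2), and their interaction". It then adds a fallback: "if model assumptions are violated, change scores between T1 and T2 will be calculated and compared between groups", by t-test or Mann–Whitney test. The only decision criterion is general: p "<0.05 will be considered significant in all analyses". No contrast within the mixed model is named, and no rule says what result would count as maintenance.

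**The concern.** The clinical question concerns one quantity: is there still a difference between the arms at T2? In the model described, the only listed term that carries a treatment effect over time is the group-by-time interaction. With time at three levels, this is a 2-degree-of-freedom test that the arm difference is the same at all three visits. A difference at T1 alone makes that hypothesis false. A significant interaction is therefore compatible with an effect that persisted, one that vanished, or one that appeared only late.

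The fallback asks something else again. Its null is that the arm difference did not change from T1 to T2. A significant result there speaks against simple maintenance, and a non-significant one in a trial this small says little.

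At stake is the reading of the T2 result. A significant interaction could be taken as persistence when only the T1 difference drove it. In addition, the T2 estimate available from the mixed model is not of the same kind as the T1 estimate, although the pilot is meant to supply effect size and variability for a definitive trial.

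**Working it through.** **Inputs from the protocol.** Two arms, allocated "with an allocation ratio of 1:1"; 12 per arm (10 raised for dropout); visits at baseline, T1 and T2; significance level 0.05, taken as two-sided. The protocol gives no operating figure for the T2 analysis, so there is none to reproduce.

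**Assumptions.** The protocol gives no SD, no within-patient correlation and no number for its medium effect. I set SD = 1, correlation ρ = 0.3, 0.5 or 0.7, and arm effect d = 0.5, 0.8 or 1.0 SD. Data are complete unless stated.

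**Step 1: non-centrality of the interaction test.** With n per arm and random intercepts (equal variances, equal correlation), the interaction F test has 2 and 2(2n − 2) degrees of freedom and non-centrality

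λ = (n/2) × Σ(d_j − d̄)² / (1 − ρ),

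where d_j is the arm difference at visit j.

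- Effect kept: differences (0, d, d), mean 2d/3. Sum of squares = 4d²/9 + d²/9 + d²/9 = 2d²/3.
- Effect lost: differences (0, d, 0), mean d/3. Sum of squares = d²/9 + 4d²/9 + d²/9 = 2d²/3.
- Effect only at T2: differences (0, 0, d) again give 2d²/3.

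λ is identical in all three cases, whatever d, ρ or n.

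**Step 2: numbers.** For n = 12 and ρ = 0.5, λ = 6 × (2d²/3) / 0.5 = 8d², on 2 and 44 degrees of freedom.

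| d | λ | Interaction significant, effect kept | Interaction significant, effect lost |
|---|---|---|---|
| 0.5 | 2.00 | 21.3% | 21.3% |
| 0.8 | 5.12 | 48.5% | 48.5% |
| 1.0 | 8.00 | 68.6% | 68.6% |

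At d = 0.8 and ρ = 0.7 both are 71.6%. Simulation at d = 0.8 and ρ = 0.5 gave 48.6% kept and 48.8% lost. With 17% or 30% of patients missing T2 equally in both arms, λ falls to 4.93 or 4.77 (d = 0.8, ρ = 0.5) but stays equal for kept and lost.

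**Step 3: departure from compound symmetry.** If the true correlation is first-order autoregressive (0.5), the same test rejects in 41.4% (kept) and 43.4% (lost) at 12 per arm and d = 0.8. Exact equality goes, but the shift is towards the lost effect.

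**Step 4: the fallback.** The T1-to-T2 contrast at n = 12, d = 0.8, ρ = 0.5 rejects in 5.0% if the effect is kept and 48.3% if it is lost. This uses the mixed model's error variance; a plain t-test on 22 degrees of freedom would do slightly worse. So 100 − 48.3 = 51.7% of trials with a wholly lost effect would show no significant change.

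**Step 5: the T2 contrast inside the planned model.** The T2-versus-baseline contrast does separate the cases: at d = 0.8 and ρ = 0.5 it rejects in 48.3% if kept and 5.0% if lost. But it estimates change from baseline. Per patient, a change score has variance 2(1 − ρ), and the baseline-adjusted outcome has variance 1 − ρ² in large samples. The ratio is 2(1 − ρ)/(1 − ρ²) = 2/(1 + ρ), which is 1.54, 1.33 and 1.18 at ρ = 0.3, 0.5 and 0.7.

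**Step 6: baseline-adjusted T2 comparison.** By simulation at 12 per arm, ANCOVA at T2 rejects in about 5% when the T2 effect is zero, whatever the T1 effect. With d = 1.0 kept at T2:

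| ρ | ANCOVA at T2 | T2-versus-baseline contrast | Interaction |
|---|---|---|---|
| 0.5 | 75% | 67% | 69% |
| 0.3 | 67% | 53% | 53% |

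**The case against.** The strongest reply is that the protocol names a model, not a test. It nowhere says that maintenance will be declared when the overall interaction is significant. A three-level interaction has two coefficients, one of which can be the T2-versus-baseline contrast, and Step 5 shows that this contrast does discriminate. Choosing the contrast is often left to an analysis plan, which is not shown here. The fallback also suggests that the authors think of maintenance as what happens between T1 and T2, and a rule that significance means maintained does not fit that.

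Most of this stands. A reader might infer that the protocol commits to the overall interaction as its maintenance rule, or that the model cannot answer the persistence question; the text supports neither. A reader might also set the 21%, 49% and 69% against a nominal 5% and call them inflated type I error. They are not: a true T1 effect makes the parallel-profile null false, so those rejections are correct. Nor does the protocol state a null of no arm difference at T2; that is inferred from its words on maintenance and persistence. Exact equality of the rates needs compound symmetry. The change-from-baseline contrast is valid under randomisation, and its loss is one of precision only.

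What the reply does not remove is the mismatch within the protocol's own text. It goes beyond the model to fix a fallback, and the overall interaction and the fallback test different hypotheses, neither of which is persistence. With p below 0.05 as the sole criterion, significance could be read in favour of maintenance under one route and against it under the other.

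**Conclusion.** The point holds in a limited form. If the overall interaction is read as the test of maintenance, it cannot tell a kept effect from a lost one. Under the random-intercept model's own assumptions that equality is exact and does not depend on the assumed effect, correlation or sample size; only the illustrative percentages do. The fallback reverses the meaning of significance, so interpretation would depend on an assumption check. The model's T2-versus-baseline contrast would answer the question, but it is not named, and it is less precise than the adjustment already used at T1 (variance ratio 1.18 to 1.54 for ρ from 0.7 to 0.3).

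The consequence is modest. This is a pilot of 24 patients meant to inform a later trial, T2 is not the primary time point, and the T1 comparison is unaffected. The change is still worth making before the data are analysed.

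**What to change.** State in the Statistical analysis section that the T2 conclusion rests on the single between-arm difference at T2, adjusted for baseline, with its 95% CI, and not on the overall group-by-time interaction or the T1-to-T2 change test.

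Obtain it in one of two ways:

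- an ANCOVA at T2; or
- a mixed model with T1 and T2 as outcomes, and baseline score, its interaction with time, group, time and group-by-time as fixed effects, taking the group contrast at T2.

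With complete data the point estimates agree; the standard errors may differ if the mixed model pools residual variance over visits.

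If assumptions fail, use a non-parametric baseline-adjusted comparison at T2, so that the fallback addresses the same question. Report the T1 and T2 adjusted differences side by side, and speak of maintenance only when an effect was shown at T1 and the T2 difference is itself supported.

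The cost is a change of wording and one contrast in the existing software, with no extra patients or data. The downside is that a claim of maintenance becomes harder to reach if the effect fades.

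### The T2 fallback tests T1-to-T2 change between arms, a contrast that is zero whether the benefit is kept or never existed, so a non-significant result cannot support maintenance

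*Protocol article*

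**What the plan says.** All references are to the protocol article.

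- **Aim at T2.** Outcome measures, on the MASA and the endoscopic scale: "The same scales will be used at T2 to measure the maintenance of the effect". The Discussion repeats the aim: "The persistence of treatment benefits will be assessed at follow-up (T2), conducted 2 months after the conclusion of acupuncture therapy". It adds of this period, "during which patients will continue to receive standard rehabilitation care".
- **Planned analysis.** Statistical analysis: a linear mixed model with random intercepts, "including group, time (baseline, T1, T2), and their interaction as fixed effects".
- **Fallback.** The same sentence continues: "if model assumptions are violated, change scores between T1 and T2 will be calculated and compared between groups using independent" t-tests or Mann–Whitney tests.
- **Decision rule.** The only one given is a p-value "<0.05 will be considered significant in all analyses". The article states no margin for maintenance, no equivalence or non-inferiority criterion and no confidence-interval rule. It does not say what a significant or a non-significant fallback result would mean.

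**The concern.** Maintenance is a statement about the treatment effect at T2: is the advantage seen at T1 still there? The mixed model contains baseline, T1 and T2, so it can yield the between-arm contrast at T2 relative to baseline. The fallback leaves out baseline and asks whether the arms moved differently after T1. Its null hypothesis, no between-arm difference in T1-to-T2 change, is exactly the state of full maintenance. A significance test cannot establish its own null.

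The same null also holds if the intervention never worked. What is zero in both cases is the between-arm difference in change, not the change itself, because both arms continue rehabilitation and may improve.

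If the fallback is used, the T2 objective is addressed by a test that cannot show persistence, and the pilot supplies no estimate of the T2 effect for planning the definitive trial.

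**Working it through.** **1. What the fallback estimates.** Let E1 and E2 be the between-arm differences in mean score at T1 and T2. The between-arm difference in mean T1-to-T2 change is E2 − E1.

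- Benefit fully kept: E2 = E1, difference 0.
- Never a benefit: E1 = E2 = 0, difference 0.
- Benefit fully lost: E2 = 0, difference −E1.

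The first two states give p ≥ 0.05 in 95% of trials, so the test cannot tell them apart.

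**2. Inputs from the article (Statistical analysis).** The significance level is 0.05. The pilot needs 10 per arm, raised to 12 for dropout. A medium effect is hypothesised for the main trial, which is put at 34 to 176 per arm for 80% power.

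**3. Reproducing the article's figures.** A two-sided t-test at 0.05 with 80% power needs 176 per arm at d = 0.3 and 34 at d = 0.7, so the stated range is reproduced. Raising 10 to 12 corresponds to 10/(1 − dropout) for dropout of about 10% (11.1, rounded up) to 16.7% (12.0). The 10 per arm is a cited rule of thumb and cannot be derived from the article.

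**4. Assumptions, not in the article.** Two-sided testing; equal SDs at all visits; correlation ρ between visits of 0.5, 0.7 or 0.9; T1 effect D = 0.5 SD as an illustration within the 0.3–0.7 range, with D = 1.0 SD for contrast.

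**5. Formula.** The SD of a change score is SD × √(2(1 − ρ)). If the T1 effect is wholly lost, the standardised difference in change is D/√(2(1 − ρ)). For D = 0.5:

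- ρ = 0.5: 0.5/1.000 = 0.50
- ρ = 0.7: 0.5/0.775 = 0.65
- ρ = 0.9: 0.5/0.447 = 1.12

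The noncentrality is this value × √(n/2), with 2n − 2 degrees of freedom.

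**6. Probability that the fallback is non-significant (noncentral t).**

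| True state | n per arm | ρ = 0.5 | ρ = 0.7 | ρ = 0.9 |
|---|---|---|---|---|
| Fully kept, or never an effect | 10 or 12 | 95% | 95% | 95% |
| 0.5 SD, half lost | 10 | 92% | 89% | 78% |
| 0.5 SD, half lost | 12 | 91% | 88% | 74% |
| 0.5 SD, all lost | 10 | 82% | 72% | 34% |
| 0.5 SD, all lost | 12 | 78% | 67% | 26% |
| 1.0 SD, all lost | 10 | 44% | 22% | 0.3% |
| 1.0 SD, all lost | 12 | 35% | 14% | 0.1% |

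Simulation agrees with these values to within about one percentage point.

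**7. Would a confidence interval on the same contrast rescue it?** The 95% half-width is about 0.85 SD of the change score at 12 per arm and 0.94 at 10. Multiplying by √(2(1 − ρ)) puts it on the score scale. At 12 per arm this is 0.85, 0.66 and 0.38 SD for ρ = 0.5, 0.7 and 0.9; at 10 per arm it is 0.94, 0.73 and 0.42. An observed difference of exactly zero would exclude loss of a 0.5 SD effect only at ρ = 0.9.

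**8. A contrast aimed at T2.** As a simple reference, compare T2 minus baseline between arms. With a fully maintained 0.5 SD effect, its power is 22%, 33% and 75% at 12 per arm, and 19%, 28% and 66% at 10 per arm, for the three correlations. With no effect at T2 it rejects in 5%. Power remains low unless ρ is high, but the estimate is of the effect at T2, so presence and absence of an effect at T2 are different states of this contrast.

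**The case against.** Several points on the other side have force.

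- **Interpretation.** A reader might infer that a non-significant fallback would be reported as success. The article does not say so; it states no reading of that result. What stands is narrower: the result could not support maintenance if it were offered as support.
- **The T1 result is known.** T1 is analysed separately by baseline-adjusted ANCOVA, so a reader would see if there was no effect to maintain. This limits confusion with the never-effective state. It does not help separate an effect that was kept from one that was lost without being detected.
- **The mixed-model contrast is not named.** The T1-to-T2 difference in change is one component of the group-by-time interaction, so the two routes need not differ. That is fair, and the choice can be left to an analysis plan. But the model can supply a T2-versus-baseline contrast, while the fallback as written cannot.
- **Low power belongs to the pilot.** This is correct: step 8 of the working shows it for a T2-directed contrast too. The main defect is the choice of contrast, which more patients would not cure.
- **The size depends on assumptions.** It does. At ρ = 0.9, or with a large lost effect, loss would often be detected.

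Three wider criticisms are tempting but not supported. The alternative at T1, "or non-parametric alternatives, if assumptions are not met", names no method and may well be baseline-adjusted. A mixed model with a free group term at baseline is a standard choice, and preferring a constrained version is a matter of taste. Shapiro–Wilk is named for describing continuous variables, not as the check that triggers this fallback.

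**Conclusion.** The point holds for the T2 fallback alone. The named contrast is E2 − E1, which has the same value under full maintenance and under no effect at any time, and it does not estimate the effect at T2. This conclusion needs no numerical assumption.

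The size does. For an assumed 0.5 SD effect wholly lost by T2, with equal SDs and two-sided alpha 0.05, the fallback misses the loss in about 67–82% of trials at correlations of 0.5–0.7, and in about 26–34% at 0.9, with 10 to 12 per arm. The article gives no SD, correlation or numerical effect size, so these figures are illustrations.

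The point should be fixed but does not threaten the trial. The analysis is a contingency, applies at follow-up and sits in a declared pilot. The primary T1 comparison is untouched.

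**What to change.** In the Statistical analysis section, replace the T1-to-T2 change-score fallback with a between-arm comparison of T2 scores adjusted for baseline. If model assumptions fail, use rank ANCOVA or a permutation ANCOVA. Report, for the MASA and for the Pooling score, the T2 difference with its 95% CI beside the T1 difference, so that persistence is judged from the two estimates together.

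Add one sentence: a non-significant between-arm comparison of T1-to-T2 change is not evidence of maintenance. If that change is still of interest, present it descriptively, with its CI.

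The cost is a few lines of wording and of analysis code. Baseline, T1 and T2 scores are already scheduled, so no new data, visits or patients are needed.

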It should be noted, however, that patient cooperation is not necessary to achieve oral feeding. Several studies have examined the impact of cognitive level on oral feeding recovery (15). While a cognitive threshold equal to or higher than level 4 on the Rancho Los Amigos Cognitive Functioning Scale (LCF) was initially deemed necessary (2), more recent studies have extended the possibility of oral feeding recovery to patients in a minimally conscious state (16, 17). According to the latest evidence, only patients with unresponsive wakefulness syndrome are very difficult, if not impossible, to rehabilitate with respect to dysphagia (18, 19). Another factor closely related to swallowing that should be taken into consideration during dysphagia rehabilitation in this patient population is the presence of a tracheal tube. Fifty to 70 % of patients with sABI are tracheotomized at the time of transfer to the IRU (4), and its presence has been shown to be closely related to dysphagia in a bidirectional manner (20–22). Tracheotomy can affect the physiology of swallowing, while impaired saliva management and persistent dysphagia remain major obstacles to successful decannulation, even in the long term (23). The inability to swallow saliva can lead to iatrogenic sialorrhea or excessive saliva accumulation (24), resulting in stagnation in the oral cavity that promotes excessive salivation, skin irritation, choking, impaired oxygenation, and even life-threatening pneumonia (25).

Given the clinical complexity and heterogeneity that characterizes this population, the rehabilitation of dysphagia in patients with sABI outcomes represents a considerable challenge (26).

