#### Inclusion criteria

Time between acute event and enrolment <3 months.Age >18 years.Presence of tracheal cannula at study enrollment.Signature of informed consent by legal representative.

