### Clinical and instrumental assessments

Assessments will be performed at recruitment (T0), after the 4 weeks (T1) and after 12 weeks (T2).

Clinical evaluation (planned at T0, T1 and T2) will be supported by the clinical scales recommended by the Italian Society of Physical and Rehabilitation Medicine (41) and includes the CRS-R and the LCF, the Disability Rating Scale (DRS) and the Functional Independence Measures (FIM). Dysphagia will be assessed by the Mann Assessment of Swallowing Ability (MASA) Scale and the FOIS. At T2, the Glasgow Outcome Scale-Extended (GOSE-E) (42) will be performed.

The instrumental evaluations will include the Fiberoptic Endoscopic Evaluation of Swallowing (FEES) (43) integrating the compilation of the Pooling score.

To identify possible confounding factors such as Epileptic status and Intensive Care Unit-Acquired Weakness may interfere with the swallowing function, other data will be recorded from instrumental exams included in the routinary clinical practice (standard electroencephalography-EEG and Electroneuro/myography-ENG/EMG) (44).

Finally, the decannulation achievement and its timing and the infection rate will be recorded.

For the purposes of this study, infections will be recorded as clinical events requiring initiation or escalation of systemic antibiotic therapy supported by clinical signs and, when available, microbiological sampling. Pneumonia will be recorded when respiratory infection is the primary suspected source and is supported by: (i) new or progressive and persistent pulmonary infiltrate/consolidation on chest imaging; (ii) at least two of the following: fever or hypothermia, leukocytosis/leukopenia, purulent respiratory secretions or increased suctioning needs, worsening gas exchange/increased oxygen requirement, or new/worsening cough/dyspnea/tachypnea; with (iii) microbiological support when available (e.g., positive culture from respiratory secretions).

All evaluations will be performed by professionals blinded to the treatment/control arm. Moreover, patients enrolled in the study, given their state of unconsciousness and behavioral/cognitive confusion, may be considered blinded for the purpose of the received AA treatment.

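### Decannulation time is tested both by t-test/Mann–Whitney and by Kaplan–Meier with no stated priority, and the first cannot use patients who are still cannulated

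*Protocol article*

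**What the plan says.** Under Outcome measures, the first secondary outcome is "improvement on the decannulation rate and/or reduction in decannulation timings at T1 and T2". The Statistical analysis section gives it two kinds of comparison.

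- **Rate:** "decannulation rates at T1 and T2 will be compared between groups using chi-square or Fisher’s exact tests".
- **Time:** "decannulation times will be compared using independent" t-tests or "Mann–Whitney U tests and Kaplan–Meier survival analysis".

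The section does not say which patients enter the t-test or Mann–Whitney, what value a patient who is never decannulated receives, or which of the two time analyses decides. It applies the 0.05 threshold to all analyses. The intention-to-treat statement is made for the primary analysis.

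Three other statements bear on the point. Every patient enters with a cannula (Inclusion criteria: "Presence of tracheal cannula at study enrollment"). Assessment ends at 12 weeks, T2 (Clinical and instrumental assessments). The Introduction expects incomplete decannulation, since impaired saliva management and "persistent dysphagia remain major obstacles to successful decannulation, even in the long term".

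**The concern.** A patient who still has the cannula at the visit has no decannulation time. Without a rule that assigns one, a t-test or Mann–Whitney can be run only on those already decannulated. Membership of that group is decided after randomisation by the event that acupuncture plus auriculotherapy (AA) is meant to make more frequent, so the two subsets are no longer randomised groups.

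If AA makes harder cases decannulable, those patients are likely to be late. They enter the AA mean, while their counterparts in the control arm are left out. The comparison can then look null, or favour control, although AA works.

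Kaplan–Meier does not have this fault, but it stands beside the other tests with no order of precedence. The outcome itself is worded as rate and/or timing. The report could therefore carry two significance statements on decannulation time that disagree, with nothing fixed in advance to settle which counts.

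**Working it through.** The protocol states no decannulation rate, median time, hazard ratio or power, so there is no figure to reproduce. All decannulation rates and timings below are assumptions. From the document: 12 per arm, 1:1 allocation, horizon H = 12 weeks = 84 days, threshold 0.05 (taken as two-sided).

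**1. Proportional benefit.** Assume constant hazards with p = 30% (control) and 60% (AA) decannulated by day 84.

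- Hazard: λ = −ln(1 − p)/H. Control 0.3567/84, so 1/λ = 235.5 days. AA 0.9163/84, so 1/λ = 91.7 days. Hazard ratio 0.9163/0.3567 = 2.57.
- Mean time among the decannulated: 1/λ − H(1 − p)/p. Control 235.5 − 84 × 0.7/0.3 = 39.5 days. AA 91.7 − 84 × 0.4/0.6 = 35.7 days. Difference 3.8 days.
- Restricted mean time with cannula, all patients: p/λ. Control 0.3 × 235.5 = 70.7 days. AA 0.6 × 91.7 = 55.0 days. Difference 15.6 days (from unrounded values).

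Restriction to the decannulated leaves about a quarter of the benefit (3.8/15.6).

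**2. Power at 12 per arm, by simulation.** Significance is counted in favour of AA. A trial with fewer than two decannulated patients in an arm counts as not significant for the t-test.

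| Assumed 12-week rates | t-test, decannulated only | Log-rank, all randomised | Wrong direction: mean of decannulated | Wrong direction: log-rank |
|---|---|---|---|---|
| 30% v 60% | 4% | 33% | 42% | 6% |
| 40% v 70% | 6% | 33% | 38% | 5% |

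**3. Benefit made up of late decannulations.** Two versions. In each, 30% of both arms are decannulated with the same timing, and AA adds a further 30%.

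- Shared 30% around week 5, extra 30% around week 9. Control mean 5.0 weeks; AA mean (0.3 × 5 + 0.3 × 9)/0.6 = 7.0 weeks. The t-test is significant in favour of control in 19% of trials at 12 per arm.
- Shared 30% timed as the control arm in step 1 (mean 39.5 days), extra 30% uniform on days 42–84 (mean 63 days). AA mean (39.5 + 63)/2 = 51.3 days, about 12 days later than control. The t-test is significant in favour of control in about 12% of trials at 12 per arm.

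In both versions AA reduces total time with a cannula. In the second, the restricted mean is 70.7 days for control against 0.3 × 39.5 + 0.3 × 63 + 0.4 × 84 = 64.4 days for AA.

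**4. At T1.** The outcome is also to be read at T1. Under step 1, the proportion decannulated by day 28 is 1 − 0.7^(1/3) = 11% for control and 1 − 0.4^(1/3) = 26% for AA, or about 1 and 3 of 12 patients. A test on observed times then has almost no data.

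**The case against.** The strongest reply is that the plan does not rely on the t-test. The same sentence adds Kaplan–Meier, which keeps patients still cannulated at T2 as censored, and the rate comparison sits beside it. In the scenarios above both would tend to show more decannulation with AA, next to any misleading mean. This stands. A reader who stops at the first half of the sentence might infer that the plan as a whole ignores censoring, and the text does not support that.

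It is also true that the protocol never says the t-test is limited to decannulated patients. That is an inference. It is the natural one, because no time is assigned to anyone else.

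Two further extensions are tempting and should not be made.

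- **Death.** A reader might object that Kaplan–Meier would censor deaths. The effect is small: a Kaplan–Meier estimate of 30% corresponds to a cumulative incidence of 29.3%, 28.6% or 27.1% at an assumed mortality of 5%, 10% or 20%. Such detail may also sit in an analysis plan that is not shown.
- **Infections.** A reader might carry the criticism over to the infection rates. These can be read as the proportion of patients infected by fixed visits, for which chi-square or Fisher's exact test is valid.

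Finally, this is a secondary outcome in a pilot meant to size a later trial, and even log-rank has only about 33% power under the assumed effects.

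What the reply does not remove is that a test which can point the wrong way is listed on equal terms with one that does not share this fault, with no rule to choose between them.

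**Conclusion.** The point holds in limited form. Two analyses that can disagree are set for one secondary outcome without precedence, and the t-test/Mann–Whitney is unsuited to an event that many patients may not reach by 12 weeks.

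Under the assumed 30% v 60%, it shrinks a 15.6-day benefit to 3.8 days and has about 4–6% power against 33% for log-rank at 12 per arm. When the benefit comes as late decannulations, it is significant for harm in roughly 12–19% of trials, depending on the assumed timings.

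These figures rest on assumed decannulation rates and timings and on reading the test as restricted to decannulated patients. Severity is modest. The primary outcome (MASA and Pooling score) is untouched.

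**What to change.** In the Statistical analysis section, delete the t-test/Mann–Whitney as a between-group test of decannulation time. State that time runs from randomisation, in all randomised patients, censored at T2, and that the survival analysis is the only comparison of time. Name one form in advance:

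- Kaplan–Meier with a log-rank test; or
- cumulative incidence with death as a competing event; or
- the difference in restricted mean time to day 84 with a 95% confidence interval.

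Report times among decannulated patients by arm as description, without a p-value. The rate comparisons at T1 and T2 can stay as they are.

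The cost is wording only. Decannulation and its timing are already recorded, and neither the sample size nor the visit schedule changes.
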